**Figure 1 figure1:**
[figure not shown]
Phase 2 pilot randomized controlled trial overview. CASI: computer-assisted self-interview; iMI4HIV: internet-based Motivational Interviewing training program for HIV CSS; MI: Motivational Interviewing; QI: qualitative interview.

#### Recruitment of CSS

We will work with HIV care clinics associated with the NECA AETC and CHW training program partners to enroll 30 CSS in the RCT. Interested CSS will be instructed to contact the study research assistant who will screen them for eligibility. Eligibility criteria will be as described above for the phase 1 CSS participants. If these criteria are met, research staff will send them an “enrollment email,” which will include a link to an online informed consent form.

Our assessment of acceptability of iMI4HIV will be guided by the Theoretical Framework of Acceptability [95] (TFA; refer to components in Textbox 2), which was derived from a review of the literature on acceptability, and views acceptability as “a multi-faceted construct that reflects the extent to which people delivering or receiving a healthcare intervention consider it to be appropriate, based on anticipated or experienced cognitive and emotional responses to the intervention” [95]. The TFA has guided qualitative and mixed methods research on the acceptability of health care interventions among patients and providers [96-99]. The TFA’s 7 domains have informed the development of a generic TFA quantitative assessment with Likert-type items to assess each component of the model [100].

Components of the Theoretical Framework of Acceptability.
**Theoretical Framework of Acceptability construct definitions**
• Affective attitude: how the individual feels about the intervention• Burden: perceived amount of effort that is required to participate in the intervention• Ethicality: the extent to which the intervention has a good fit with an individual’s value system• Intervention coherence: the extent to which the participant understands the intervention and how it works• Opportunity costs: the extent to which benefits, profits, or values are given up to engage in the intervention• Perceived effectiveness: the extent to which the intervention is perceived as likely to achieve its purpose• Self-efficacy: the participant’s confidence that they can perform the behaviors required to participate in the intervention

#### Baseline Assessments

After enrolling, participants will receive an email with a link to the CASI to be completed within 7 days and will be scheduled for their SPI-Baseline session, which will be audio-recorded and rated for MI fidelity. The CASI and the SPI-Baseline must be completed prior to the MI workshop. The baseline CASI assessment will include the following:

Demographics. This will capture information on age, gender, race, ethnicity, education, primary language, counseling training, and prior MI training.MI Knowledge and Attitudes Test (MIKAT) [101], a 29-item assessment that has shown sensitivity to detect change in MI consistent and inconsistent behavior in pre- and posttraining comparisons [101-104], with acceptable internal consistency [104]. The MIKAT will be adapted to diminish its focus on MI for substance use treatment.Perceptions of Evidence-Based Practices (EBPs) will be evaluated using 4 self-report measures:The Evidence-Based Practice Attitudes Scale-15 [105] is a 15-item assessment of providers’ attitudes toward EBPs, with 4 factors: Appeal, Requirements, Openness, and Divergence. Participants will also complete 2 assessments of their perceptions of how EBPs are viewed by their supervisor and at the agency.The Implementation Climate Scale [106], reliably assesses the extent to which a clinic fosters EBP implementation.The Implementation Leadership Scale [107] assesses leadership support for EBP implementation.TFA quantitative questionnaire [100]. Finally, we will assess the prospective acceptability of iMI4HIV using a tailored version of the generic TFA questionnaire. This questionnaire is composed of a 5-point Likert-type scale for each of the TFA components and 1 general question on acceptability. Findings from phase 1 will also identify other areas of inquiry for the baseline CASI.SPIs. We will use scheduling software for study participants to schedule their SPIs. At the specified time, the SPI actor will contact the participant by phone to conduct a 15-minute MI session focused on an HIV care scenario. The session will be audio-recorded and then rated using the Motivational Interviewing Treatment Integrity ratings (MITI 4.2) [108], a valid and reliable measure of MI skills [109]. MI skills will be assessed at baseline, postworkshop, post iMI4HIV, and 3 months later (for participants randomized into iMI4HIV).

#### MI Virtual Workshop

Synchronous VMI workshops will be conducted through Zoom (Zoom Video Communications, Inc). We expect 2 to 3 workshops with 10-15 CSS in each to facilitate individualized feedback during the workshops. Afterward, participants will receive a brief survey asking for feedback on the workshop.

#### Randomization

As shown in Figure 1 above, after completing the SPI-2, participants will be randomized into iMI4HIV or waitlist control at a 2:1 ratio. After completing the VMI workshop, iMI4HIV participants will be sent a link to set up their account and access iMI4HIV. They will be asked to complete the online training within 4 weeks. Participants will receive weekly reminders to complete the training within 4 weeks, at which time access to the program will end. Waitlist control individuals will not have access to iMI4HIV during the 4 weeks following the VMI workshop but will get access once their follow-up assessment and SPI-3 are completed.

#### Follow-up Assessment 1

Four to 5 weeks after randomization, participants in both arms will complete the first follow-up assessment, which forms the basis for comparing the 2 RCT arms and will consist of a CASI and SPI #3. Participants in the iMI4HIV arm will also take part in a QI. Participants in the iMI4HIV arm who did not complete the program will still be invited to complete the follow-up assessment (for which there is an incentive) so we can learn about obstacles to completing the program and obtain their recommendations.

Follow-up CASI. This assessment will repeat those measures conducted at baseline but tailored to each study arm. For the intervention arm, the follow-up CASI will additionally include iMI4HIV-specific assessments: (1) TFA-based questions to assess acceptability of iMI4HIV, (2) obstacles to completing iMI4HIV, and (3) self-report of any additional MI training (eg, watching YouTube videos and reading MI articles or books) in which participants engaged. Findings from phase 1 will also identify other areas of inquiry for the follow-up CASI.SPI-3. After completing the follow-up CASI, participants in both arms will complete the third SPI as previously described, but using a different HIV-related patient scenario.QIs with CSS. Participants in the iMI4HIV arm will then have a QI to explore topics including (1) the TFA constructs, (2) iMI4HIV components deemed enjoyable, educational, and helpful, (3) acceptability of different gamification components, (4) facilitators and obstacles to completing iMI4HIV, (5) perceptions of current competency in MI, including strengths and weaknesses, (6) factors that have facilitated or hindered the use of MI in HIV care interactions, and (7) recommendations for further revisions of iMI4HIV. QIs are expected to be approximately 60 minutes in duration, and will be audio-recorded, transcribed, and verified for accuracy before being deidentified and uploaded to NVivo (Lumivero) for coding and analysis.

#### Follow-up Assessment 2

The second follow-up assessment will vary based on the study arm. Once participants in the control arm have completed their Follow-up Visit 1, they will be given access to iMI4HIV. They will be asked to complete the program within 4 weeks, at which point they will complete Follow-up Visit 2, consisting of (1) follow-up CASI assessment, (2) SPI-4, and (3) a QI. This follow-up CASI will be the same as that completed by participants in the active iMI4HIV arm at their first follow-up assessment. The SPI-4 will use a different scenario from those used in previous SPIs and will be conducted using the same procedures as the baseline SPIs. The QI will use the same as guide for the first follow-up assessment for those in the iMI4HIV arm; however, it will include additional questions exploring the impact of delayed access to iMI4HIV after completing the virtual workshop. Intervention arm participants will complete their Follow-up Visit 2 three months after their Follow-Up Visit 1. The assessment will repeat the CASI assessment from the first follow-up assessment and they will complete SPI-4. This will allow us to explore the degree to which gains in MI skills at SPI-3 are retained after 3 months.

### Data Analysis

#### Qualitative Data Analysis for QIs

Transcripts from the phase 2 QI audio-recordings will be reviewed for accuracy and uploaded into NVivo for management and analysis. Codebook development will begin when 8 transcripts are available. First-level codes will be guided by the TFA components, while second- and third-level codes will emerge from themes identified in the narratives. An initial set of codes will be generated independently by 2 research staff, compared, then synthesized to compile shared coding categories and subcategories, all with definitions, inclusion and exclusion criteria, and examples. As transcripts become available, coding will continue, refining definitions that will be used to process the remainder of the manuscripts. Coders will discuss discrepancies until they achieve 80% intercoder convergence. As per Patton [110], we will identify indigenous (ie, participant-generated) as well as analyst-constructed typologies. Once data are coded, analysis of coding reports will include categorization, abstraction, comparison, integration, iteration, and refutation of themes.

#### Integration of Quantitative and Qualitative Data

We will exploit the richness of our mixed methods approach, with quantitative and qualitative findings enriching each other. Quantitative assessments allow us to systematically explore variables of interest across all participants. Qualitative data will add nuance and new insights to quantitative findings. During data analysis, interpretation of quantitative results will be enriched by the summary of codes for specific components of iMI4HIV. In NVivo, we will categorize participants based on their responses in the quantitative assessment and use these categories to compare and contrast themes and concepts that emerge from the qualitative data.

#### Quantitative Data Analysis

##### Primary Outcomes

The primary outcomes of the pilot study will be based on the phase 2 RCT pilot, including (1) the percent of study participants that complete iMI4HIV within 4 weeks posttraining workshop (feasibility) and (2) the percentage of participants that respond Acceptable or Completely Acceptable to the question, “How acceptable was iMI4HIV to you?” from the TFA generic acceptability questionnaire (acceptability).

##### Exploratory Outcomes

We will also explore the following outcomes:

MI skills acquisition. MITI-4.2 ratings for (1) Technical Component, (2) Relational Component, (3) Percent Complex Reflections, (4) Reflection:Question Ratio, (5) Total MI Adherent, and (6) Total MI Non-Adherent. Although the pilot RCT is not powered to detect differences between the intervention and control groups, we will compare these scores between the 2 groups for the SPI-3 assessment and within groups for each of the SPI assessments.Feasibility. Metadata from iMI4HIV, including mean (1) duration to complete specific iMI4HIV tasks, (2) number of times a lesson was completed prior to achieving a passing score, and (3) score for each task.Acceptability. Mean ratings on each of the generic TFA items (Affective Attitude, Burden, Intervention Cohesiveness, Self-efficacy, Ethicality, Perceived Effectiveness, and Opportunity Cost).

Data collected via assessments will be imported into IBM SPSS Statistics to calculate descriptive statistics for the sample. Estimation of the feasibility and acceptability outcomes (primary and exploratory) will be accomplished by generating the point estimate with its corresponding 95% CI. We will use a *t* test for continuous outcomes, and Fisher exact test for binary outcomes for the above comparisons. Adjustment for covariates, if necessary, with control baseline values, will be accomplished by multiple linear (continuous outcomes) or logistic (dichotomous outcomes) regression. While this study will not recruit a large enough sample to provide adequate power for assessing the efficacy of iMI4HIV, we will use data from MITI-4 ratings to explore specific changes in MI skills (listed in exploratory outcomes, above). To examine the efficacy of the addition of iMI4HIV on MI skills, the generalized linear model with identity and logit link function will estimate model parameters and their SEs for continuous and dichotomous variables, respectively. The generalized estimating equation method, with a robust SE estimator, will account for the within-subject correlation due to repeated measures from the same participant. Accompanying each of these tests will be point and interval estimates for the parameters of interest, such as group mean differences and odds ratios.

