However, mastering MI is not easy [38-43]. MI entails adhering to standard counseling tools (ie, open-ended questions, affirmations, reflections, and summaries) with an empathic, client-centered, collaborative approach. MI also includes a more difficult, technical component—the systematic elicitation and reinforcement of change talk (statements made by clients that argue for change, eg, “I need to get better at taking my pills”) and avoiding evocation of sustain talk (statements made by clients that argue for not changing, eg, “It’s hard to remember taking my pills”). Research on MI’s mechanisms of action has shown that more change talk and less sustain talk during a session are related to better outcomes [44-46]. Also, counselor behaviors such as advising, confronting, directing, and warning clients are associated with greater sustain talk, whereas counselor behaviors such as affirming strengths or effort, emphasizing client autonomy, and being supportive are associated with increased change talk [47,48]. Thus, to facilitate behavior change, the goal of an MI counselor is to interact with the client in a manner that facilitates change talk and inhibits sustain talk [38,48].

Standard MI training often consists of a 2-day workshop (about 14 hours total) with didactic presentations and many practice and experiential exercises. After this, attendees typically demonstrate an increase in MI relational skills (eg, asking permission before sharing information and more collaborative interactions). Demonstration of MI technical skills, such as using more open-ended questions and reflections, especially complex reflections [49-52] that are key components of MI’s mechanisms of action, is less likely after a 2-day workshop. Furthermore, acquired skills tend to diminish over the following 8-12 weeks without postworkshop feedback and coaching [53-55].

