### Phase 2: Pilot RCT

#### Overview

The overall aim of phase 2 is to assess the feasibility and acceptability of iMI4HIV and prepare the necessary research infrastructure and processes for a future fully powered RCT to test its efficacy in increasing MI skills among CSS in HIV-related interactions. Thus, we will recruit 30 CSS and randomize them using a 2:1 ratio (VMI workshop + iMI4HIV vs VMI workshop + waitlist control).

Figure 1 presents an overview of the phase 2 RCT procedures, detailing an RCT with a waitlist control arm which will gain access to iMI4HIV after completion of the Follow-Up 1 assessment. This design allows us to achieve the specific aims of the study as well as gain initial insights into the effects of iMI4HIV on MI skills and how these skills may be retained after 3 months. After all participants complete a baseline computer-assisted self-interview (CASI), they will complete SPI-1, then take part in the VMI workshop. After that, they complete SPI-2 and are then randomized into iMI4HIV versus a waitlist control. After 4 weeks, all participants complete Follow-Up 1, which consists of SPI-3, a follow-up CASI, and for only those in the iMI4HIV arm a qualitative interview. This will allow us to assess the feasibility and acceptability of iMI4HIV among those who were randomized into that arm (n=20). At this assessment point, we will also explore the effects of iMI4HIV on MI skills by comparing MI fidelity ratings of the SPI-3 between the intervention and control groups.

After Follow-Up 1, those in the control arm will be given access to iMI4HIV; after 4 weeks, only this group will complete Follow-Up 2, which will consist of SPI-4, a follow-up CASI, and an in-depth interview, which will provide additional acceptability data. Participants originally randomized into iMI4HIV will undergo their Follow-Up 2 after 12 weeks (SPI-4 and CASI, no QI). This will allow us to gain insights into retention of MI skills after 3 months, a key data point for a subsequent efficacy trial of iMI4HIV in which we would want to assess maintenance of MI skills. Community-based organizations rarely offer MI coaching to staff after a training workshop. Thus, we will not offer MI coaching in either study arm to focus on assessing the preliminary effects of iMI4HIV on participants’ MI skills.

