### Conclusions

As designed, this study specifically responds to the Notice of Special Interest: Advancing Health Communication Research on HIV Prevention, Treatment and Cure (NOT-MH-21-105) announced by NIH, which includes an interest in studies that seek to “optimize effective communication and engagement practices between PLHIV and healthcare providers.” This R34 begins to address a critical need for novel approaches to train CSS in MI, a counseling or communication approach with proven efficacy in improving health care outcomes across the HIV care cascade. With its focus specifically on MI in HIV care interactions, iMI4HIV gives CSS in HIV care settings an invaluable opportunity to solidify MI skills gained during MI training workshops. Furthermore, as an asynchronous training program, iMI4HIV provides significant flexibility in when it can be completed, increasing accessibility to potential users. If findings on feasibility (≥70% of participants complete the iMI4HIV modules within 4 weeks) and acceptability (≥80% of participants rate iMI4HIV a “4” or “5” on the TFA overall acceptability rating) are favorable, we will submit a proposal for a fully powered RCT to assess the efficacy of iMI4HIV to achieve MI competence. In that study, we may even consider a study arm using an expanded version of iMI4HIV to allow for fully asynchronous MI training, which was cost-prohibitive in this study.

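### The workshop change from SPI-1 to SPI-2 falls before randomization, yet the plan as written would test it separately in the later arms of 20 and 10 instead of once in all 30

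*Protocol article*

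**What the plan says.** The Overview of Phase 2 gives the order of events. "After all participants complete a baseline computer-assisted self-interview (CASI), they will complete SPI-1, then take part in the VMI workshop". The next step is "After that, they complete SPI-2 and are then randomized into iMI4HIV versus a waitlist control". The Randomization section agrees: "after completing the SPI-2, participants will be randomized into iMI4HIV or waitlist control at a 2:1 ratio". The total is fixed in the same Overview: "we will recruit 30 CSS and randomize them using a 2:1 ratio", and the iMI4HIV arm is given there as n=20, which leaves 10 controls.

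The Exploratory Outcomes section lists six MITI 4.2 measures and then says "we will compare these scores between the 2 groups for the SPI-3 assessment and within groups for each of the SPI assessments". The same sentence makes clear which groups are meant: "Although the pilot RCT is not powered to detect differences between the intervention and control groups". The section assigns a t test to continuous outcomes for these comparisons. It separately describes a GEE model for the effect of adding iMI4HIV. A pooled estimate of the SPI-1 to SPI-2 change is not mentioned.

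**The concern.** A within-arm comparison across every SPI includes the step from SPI-1 to SPI-2, which is the workshop change. No arms exist at either time point. Everyone has had the same planned exposure, and the later allocation is random, so any difference between the two arms' workshop changes is chance. Splitting the change by arm therefore reveals nothing real. It loses precision, and it yields two workshop results that may disagree.

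The stake is modest but concerns what the pilot is for. The Power Considerations section names longitudinal response profiles among the parameters critical for planning the next trial, and the workshop step is the first part of that profile. The Background says of technical MI skills that their demonstration "is less likely after a 2-day workshop", so small to moderate workshop gains are plausible for some of the measures. The Conclusions add, for the future trial, that "we may even consider a study arm using an expanded version of iMI4HIV to allow for fully asynchronous MI training". The size of the workshop gain would be useful background to that choice.

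**Working it through.** **Inputs from the article.** N = 30 and 2:1 allocation (Phase 2 Overview); t test for continuous outcomes (Exploratory Outcomes); two-sided α = 0.05 (Power Considerations, stated there for the primary null hypotheses).

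**Assumptions.** The same α applies to the exploratory tests. The test of change is paired. Change scores are normal. All 30 have SPI-1 and SPI-2. The true gain d, in SDs of the change score, is the same for everyone. The article gives no value for d, so a range is shown.

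**1. Arm sizes.** 30 × 2/3 = 20 and 30 × 1/3 = 10, which reproduces the article's n=20.

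**2. Precision.** The 95% CI half-width for the mean paired change, in SDs of change, is t(0.975, n−1)/√n:
- n=30: 2.045/5.477 = 0.373
- n=20: 2.093/4.472 = 0.468
- n=10: 2.262/3.162 = 0.715

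The gain detectable with 80% power is 0.53 SD (n=30), 0.66 (n=20) and 1.00 (n=10).

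**3. Chance that exactly one arm is significant.** Power p comes from the noncentral t distribution with noncentrality d√n. The arms are independent, so P(exactly one) = p20(1−p10) + p10(1−p20). At d = 0.5 this is 0.565 × 0.707 + 0.293 × 0.435 = 0.527.

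| True gain d | Power n=30 | Power n=20 | Power n=10 | Exactly one arm significant |
|---|---|---|---|---|
| 0 | 0.050 | 0.050 | 0.050 | 0.095 |
| 0.3 | 0.355 | 0.247 | 0.136 | 0.316 |
| 0.5 | 0.754 | 0.565 | 0.293 | 0.527 |
| 0.6 | 0.888 | 0.721 | 0.396 | 0.546 |
| 0.8 | 0.988 | 0.924 | 0.616 | 0.401 |
| 1.0 | >0.99 | 0.989 | 0.803 | 0.204 |
| 1.2 | >0.99 | 0.999 | 0.920 | 0.080 |
| 1.5 | >0.99 | >0.99 | 0.987 | 0.013 |

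A simulation with 100,000 replicates gave 0.529 at d = 0.5 and 0.400 at d = 0.8. At d = 0.5 the usual pattern is significance in the 20-person arm only (0.399 of the 0.527).

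**4. Chance gap between the two estimates.** SE = √(1/20 + 1/10) = 0.387 SD of change. The two arms' workshop gains differ by more than 0.5 SD with probability P(|Z| > 0.5/0.387 = 1.29) = 0.197, about one pilot in five.

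**5. Sensitivity to losses.** If 20% are lost (16 and 8 analysed), exactly one arm is significant in 48% of pilots at d = 0.5, 50% at 0.8 and 33% at 1.0.

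All of these figures are per measure. Six measures are planned; they will be correlated, so the figures should not be combined as if independent.

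**The case against.** The best case for leaving the text alone is that it never names an SPI-1 to SPI-2 contrast and does not rule out pooling. Several within-arm changes that fit the sentence are properly arm-specific, such as SPI-1 to SPI-3. The choice of contrasts could be left to an analysis plan that is not shown, and the GEE could carry a common pre-randomization change. The outcomes are labelled exploratory, intervals accompany every test, and the workshop gain is not among the study aims.

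Much of this stands, and it limits the point. It does not remove it: the sentence covers each SPI within each arm, and nothing says that the pre-randomization step is handled differently.

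A reader might infer more than the documents support:
- **That the pilot's conclusions are at risk.** They are not. The primary outcomes are completion and acceptability, the go-ahead thresholds in the Conclusions use only those, and the comparison between arms is at SPI-3.
- **That the plan intends to contrast the arms' workshop gains.** No section proposes this.
- **That discordant results will be frequent whatever happens.** This depends on an unstated effect size. The 53% at 0.5 SD lies near the peak, and the risk is small from about 1.2 SD. The Background expects relational skills typically to rise after a workshop, so large gains are plausible for some measures.
- **That workshops do not raise technical skills.** The Background says such gains are less likely, not absent, and it speaks of standard two-day workshops.
- **That every within-arm change starting at SPI-1 should go.** SPI-1 to SPI-3 ends after randomization. It is the total gain under each strategy and is legitimately arm-specific.

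**Conclusion.** The point holds as a limited flaw in an exploratory analysis. As written, the within-arm rule takes in a change that is complete before arms exist, and splits one sample of 30 into 20 and 10 for no gain. The certain cost is precision: the half-width is 0.47 and 0.72 SD of change instead of 0.37, so the control-arm interval is nearly twice as wide as it need be. The conditional cost is a workshop that appears effective in one arm only. That happens in roughly 32% to 55% of pilots per measure for true gains of 0.3 to 0.8 SD, 20% at 1.0 and 8% at 1.2. The precision figures rest on 20 and 10 participants with both SPIs and on normal change scores. The discordance figures also need a paired two-sided 5% test and an assumed gain.

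**What to change.** In Exploratory Outcomes, limit the within-group sentence and add wording along these lines:

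*The SPI-1 to SPI-2 change (workshop) is estimated and tested once, as a paired mean change with 95% CI in all participants with both SPIs, or as a common pre-randomization time effect in the GEE. It is not tested separately by arm. SPI-1 and SPI-2 values by arm are descriptive. Within-arm changes that end at a post-randomization SPI (SPI-1 to SPI-3, SPI-2 to SPI-3, SPI-3 to SPI-4) are reported by arm.*

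The last two sentences matter. Restricting by-arm reporting to SPI-2 onward would drop the total change from SPI-1 to SPI-3 and remove SPI-1 from the by-arm response profiles that Power Considerations wants for planning. The change costs a few lines of analysis text and needs no new data, visits or participants. All that is given up is two separate tests of a change that cannot truly differ by arm.

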##### Power Considerations

There is some controversy regarding the use of pilot data to estimate an actual effect size [111]; clinically meaningful effect sizes should be decided based on extrinsic, clinical judgment grounds, and not based on pilot data which are too few, typically, to obtain reliable conclusions. We can use pilot data to rule out unusually large or small true effects through standard 95% CI procedures. We will confirm that extrinsic effect sizes are contained within our CIs from the pilot. We will examine the distribution of each variable and calculate summary statistics by intervention condition. We will estimate key intervention parameters with sample means and proportions together with 2-sided 95% CIs and test the primary null hypotheses at the traditional 2-sided level α=.05 (to simulate the subsequent RCT). For planning the RCT, we will also consider 1-sided 90% confidence limits for mission-critical design parameters such as SDs and reference group end point rates and proportions in the conservative direction. This is because we intend to plan the sample size for the RCT so that power will be “excellent” (at least 80% power) for the clinically relevant effect size to be specified if our estimate of SDs is at the 1-sided 90% confidence limit in the conservative direction. This strategy will make proper allowance for the limited sample size of the pilot study with its consequent uncertainties, and still yield appropriate sample sizes for the future RCT. We will examine the strength of association between our primary outcome and key variables, with the view toward seeing if stratifying on such factors (eg, age and gender) would substantially reduce variability and increase the power of a future RCT. “Mission-critical” parameters include proportions for dichotomous end points; means and SDs for continuous end points; and response profiles for longitudinal studies. Large sample sizes are not required to locate these parameters approximately, but adequately, for planning the subsequent trial, whereas testing the study hypothesis in the pilot will generally not have sufficient statistical power. Estimation of mission-critical design parameters with point and CI estimates will be very important; continuous outcome measures make it feasible to detect promising effects even in small samples. For the continuous measures, means and SDs will be estimated. For approximately normally distributed variables, an upper 1-sided 90% confidence limit for the population SD, *s_U_*, will be constructed from *s_U_* = *s* × [(n – 1)/*x*^2^_0.10,_*_n_*_–1_]^1/2^, where *s* is the sample SD and *x*^2^_0.10,_*_n_*_–1_ is the upper 10th percentile of the chi-square distribution with *n* – 1 degrees of freedom. For approximately log-normally distributed variables, a logarithmic transformation will be applied to achieve approximate symmetry and normality. For the dichotomous variable, exact binomial methods will be used.

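### The effect of iMI4HIV on MI skills has two unranked analyses, and neither commits to adjusting for SPI-2, the skill score scheduled for everyone just before randomization

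*Protocol article*

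**What the plan says.** Under Exploratory Outcomes, the protocol article lists six MITI-4.2 scores and says "we will compare these scores between the 2 groups for the SPI-3 assessment and within groups for each of the SPI assessments". The method given is a t "test for continuous outcomes, and Fisher exact test for binary outcomes for the above comparisons". Adjustment follows as an option: "Adjustment for covariates, if necessary, with control baseline values, will be accomplished by multiple linear" or logistic regression, depending on the outcome. No criterion is given for when adjustment becomes necessary.

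The same paragraph then assigns a generalized linear model, fitted by GEE with robust standard errors, to the efficacy of adding iMI4HIV. It accounts for repeated measures on each person. The article does not say which SPI occasions enter, whether an arm-by-time term is fitted, or how this model ranks against the t test.

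On timing, the Randomization section says "after completing the SPI-2, participants will be randomized into iMI4HIV or waitlist control at a 2:1 ratio", and the Phase 2 Overview gives the same order. Baseline Assessments lists the baseline and postworkshop skill measurements as separate occasions and requires the baseline SPI to be done before the workshop. The word baseline therefore points to SPI-1, not SPI-2.

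The article is open about the status of this comparison: "Although the pilot RCT is not powered to detect differences between the intervention and control groups".

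**The concern.** The question for MI skills is what iMI4HIV adds to a workshop that everyone attends. SPI-2 measures skill at exactly that point, on the same instrument as the outcome. SPI-1 precedes a workshop intended to change the score, so it is likely to be the weaker covariate.

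Three things are at stake:

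- **Precision.** With 10 controls, any variance that SPI-2 could explain is worth removing.
- **Pre-specification.** An undefined condition for adjustment, together with two unranked analyses, leaves the analyst a choice to make after seeing the data, for each of six scores.
- **Planning the later RCT.** Power Considerations uses the pilot CIs to see which effects can be ruled out and takes an upper confidence limit for the SD into the sample size. It also looks for variables, such as age and gender, that might reduce variability. The pre-randomization score on the same instrument is an obvious candidate and is not named.

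**Working it through.** **Inputs from the protocol article.** 30 participants at 2:1 ("Thus, we will recruit 30 CSS and randomize them using a 2:1 ratio"), two-sided α = 0.05, and a between-arm comparison at SPI-3. The article states no SD, effect size, power or SPI-2/SPI-3 correlation for this comparison.

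**The plan's own figure.** 30 × 2/3 = 20 and 30 × 1/3 = 10. The article's 20 in the iMI4HIV arm is reproduced.

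**Assumptions.** Results are in units of the within-arm SD of SPI-3. The correlation ρ between SPI-2 and SPI-3 is assumed from 0.2 to 0.7, and the 0.8 SD effect used for power is also assumed. All 30 are taken to complete SPI-3.

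**Unadjusted t test.** SE = √(1/20 + 1/10) = √0.15 = 0.387 SD. With t(28) = 2.048, the half-width is 2.048 × 0.387 = 0.79 SD.

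**Adjusted for SPI-2.** SE = √[0.15 × (1 − ρ²) × (1 + 1/26)], where the last factor is the price of estimating the slope. The half-width is t(27) = 2.052 times this. At ρ = 0.5: √(0.15 × 0.75 × 1.0385) = 0.342, and 2.052 × 0.342 = 0.70 SD.

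| Analysis | SE (SD) | 95% half-width (SD) | Power at 0.8 SD | Effect with 80% power (SD) |
|---|---|---|---|---|
| t test | 0.387 | 0.79 | 51% | 1.12 |
| SPI-2, ρ = 0.2 | 0.387 | 0.79 | 51% | 1.12 |
| SPI-2, ρ = 0.3 | 0.376 | 0.77 | 54% | 1.09 |
| SPI-2, ρ = 0.5 | 0.342 | 0.70 | 62% | 0.99 |
| SPI-2, ρ = 0.7 | 0.282 | 0.58 | 78% | 0.82 |

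The equivalent gain in sample size is 1/[(1 − ρ²)(1 + 1/26)] − 1, about 15%, 28%, 50% and 89% at ρ = 0.4, 0.5, 0.6 and 0.7.

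**Chance imbalance.** The SPI-2 difference between arms also has an SE of 0.387 SD, so by the normal distribution it exceeds 0.25 SD in either direction with probability 52% and 0.5 SD with probability 20%. It carries into SPI-3 in proportion to ρ, not in full. Given an imbalance above 1 SE in favour of iMI4HIV, its mean is 1.525 × 0.387 = 0.59 SD. With no true effect, the t test estimate then averages about ρ × 0.59. Simulation (20,000 runs) gives 0.18, 0.30 and 0.41 SD at ρ = 0.3, 0.5 and 0.7, against about 0 with adjustment.

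**What a conditional rule does (same simulation, ρ = 0.3, 0.5, 0.7).**

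- If adjustment were triggered by an SPI-2 difference at p < 0.10 (an assumed trigger), type I error would be 4.6%, 4.2% and 3.1%. Power at 0.8 SD would stay at 52% to 53%, so most of the gain is lost.
- If the more favourable of the two results were reported, type I error would be 6.5%, 7.4% and 8.0% per outcome.

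**Whether the GEE settles it.** A repeated-measures model could use SPI-2, but the text does not say that it does. SPI-4 needs particular care. By then the control arm has had access to iMI4HIV and is measured about 4 weeks after Follow-up 1, while the iMI4HIV arm is measured 3 months after it. A between-arm difference at SPI-4 is not the randomized contrast of iMI4HIV against no iMI4HIV.

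**The case against.** A reader might infer that the t test is the whole analysis and that pre-randomization skill is ignored. The article does not support that, because the GEE is assigned to the efficacy question and could bring in earlier SPIs. A reader might also infer that the unadjusted comparison is biased. It is not: under randomization it is unbiased, and its CI already allows for chance imbalance.

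Four further points count against the concern:

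- **Low stakes.** The outcome is exploratory. The decision to proceed, in the Conclusions, rests on at least 70% completion and at least 80% acceptability, and effect sizes for the RCT are to come from outside the pilot.
- **Uncertain gain.** Each SPI is one 15-minute call, and SPI-3 uses a different scenario, which could lower the correlation.
- **RCT planning.** An unadjusted SD would make the later sample size conservative, not wrong.
- **Place of the detail.** Covariates and model hierarchy often belong in an analysis plan that is not shown.

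The first three stand and limit the weight of the point. The fourth stands only in part: the article does not merely leave adjustment open, it fixes an unadjusted test with an undefined condition, and that rule can be improved as written.

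**Conclusion.** The point holds as a modest, nearly free improvement. Two analyses of the same effect are listed without rank, the trigger for adjustment is undefined, and SPI-2 is not fixed as a covariate in either. Always adjusting for it narrows the 95% CI half-width from 0.79 SD to about 0.77, 0.70 or 0.58 SD at assumed correlations of 0.3, 0.5 or 0.7. At about 0.2 or below nothing is gained, and at zero correlation the interval is slightly wider (0.81 SD). These figures assume 20 and 10 completers and a linear relation between SPI-2 and SPI-3. The primary outcomes, completion and acceptability, are unaffected.

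**What to change.** - Make linear regression of SPI-3 on arm and SPI-2 the lead between-arm analysis for each MITI score, always adjusted, with a 95% CI. Transform the score where it is skewed, which is most likely for the ratio and the totals.
- Delete the words *if necessary*, and name SPI-2 in place of the general reference to baseline values.
- Keep the t test as a descriptive supplement.
- State that the GEE is supportive, which occasions enter it, and that SPI-4 is not used for the randomized contrast.
- Report the SPI-2/SPI-3 correlation and the residual SD beside the raw SD, so that the RCT can be planned on either basis.

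The cost is one degree of freedom and a change of wording. SPI-2 is already in the schedule, and the article expects the pilot RCT to launch in February 2026, so the change should be made before then.
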